| 2.0 | 29-April-2024 | Participants will be recruited from the IPP and contacted via phone for a pre-screening call to give them background information on the study and associated participant                                                                                                                                                                                                                                                                                                                                                                                                                                                                                                                                                                                                                                                                                                                                       | Revised placement for chronological order; added that participant's email                                                                                                                                           |

|     |              |                                                                                                                                                                                                                                                                            |                                                                                                                                     |
|-----|--------------|----------------------------------------------------------------------------------------------------------------------------------------------------------------------------------------------------------------------------------------------------------------------------|-------------------------------------------------------------------------------------------------------------------------------------|
|     |              | responsibilities. The participant's email address will also be collected during this call if they are interested.                                                                                                                                                          | will be collected (already in script)                                                                                               |
| 2.0 | 08-July-2024 | Participants must have a physician (family doctor or psychiatrist) during their enrollment and participation in the trial. The investigator will inform the participant's most responsible physician about their participation in the trial.                               | Text added to ensure care of the participant beyond/outside of the study                                                            |
| 2.0 | 08-July-2024 | Removal of "Participants will no longer be eligible to continue the study if they miss more than one supervised PA session with their program trainer."                                                                                                                    | Text removed to reduce participant drop out                                                                                         |
| 2.0 | 08-July-2024 | Removal of diabetes as an exclusion criterion                                                                                                                                                                                                                              | Unnecessary exclusion criterion                                                                                                     |
| 2.0 | 28-Aug-2024  | Receiving treatments congruent with Canadian Network for Mood and Anxiety Treatments (CANMAT) guidelines with no changes to treatments one month before screening (28 days), during the randomized intervention phase (28 days), and during the follow-up phase (42 days). | Inclusion criteria revised to encompass changes to any treatment                                                                    |
| 2.0 | 28-Aug-2024  | At the end of their participation in the study, participants who were randomized to the control group will have access to at least one session with a PA trainer.                                                                                                          | Revised to enhance recruitment and offer participants in the control group the opportunity to also receive personalized PA training |

# 1. INTRODUCTION

## 1.1 Background and Rationale

Over 300 million people worldwide experience major depressive disorder (MDD). More than one-third of these patients will not respond to at least two antidepressant medication trials, meeting the criteria for treatment-resistant depression (TRD). As a result, alternative therapeutic modalities, such as exercise, are garnering interest. Numerous studies have reported an association between physical activity (PA) and improvements in mood and mental health in both clinical and non-clinical populations.

Prior research demonstrates that the impact of PA depends on the frequency, intensity, and domain. The optimal dose of PA (i.e., frequency, intensity, duration, and domain) has yielded mixed results. Some studies have found light-intensity to be just as effective as moderate-intensity PA. However, others have found an association between low-intensity PA and lower prevalence of depressive symptoms, but not moderate- or vigorous-intensity PA. Low doses and enjoyability associated with PA may play a more significant role in the protective effect of PA on mental health and well-being. In line with this, a recent review suggested that self-selected intensity may have a greater protective effect on depression symptoms.

The mechanism underlying the antidepressant effect of exercise is multifaceted. Physiologically, exercise activates the endocannabinoid system, and modulates endorphin, neurotrophin, and monoamine levels to improve cognitive deficits and affective symptoms of depression. Exercise induces the release of brain-derived neurotrophic factor, which promotes brain neurogenesis and contributes to a reduction in depressive symptoms and improvement in cognitive functioning. In doing so, PA diverts an individual's attention away from negative preoccupations and improves perceptions of self-efficacy and self-concept to ultimately contribute to an improvement in treatment outcomes as well. To be more specific, regular PA participation can give individuals a sense of mastery and allow them to experience new bodily sensations such as an improved body image, sense of achievement, and feelings of control that may successfully distract them from their negative thoughts and reduce depressive symptoms.

Despite the wide-reaching benefits of PA for mental health, few studies to date have examined the role of PA in reducing depression symptoms in adult TRD patients. These studies demonstrate the need for supervision and personalization in exercise interventions for patients to optimize mental health outcomes for each individual. By acknowledging and incorporating individual PA preferences and priorities, we can increase PA frequency via enhanced motivation and engagement and thus contribute to improvements in mental health. In addition, a recent systematic review identified that the quality of research reporting and conduct across randomized controlled trials (RCT) relating to exercise interventions was suboptimal compared to that of pharmacological RCTs, thus demonstrating a need for higher quality research. As a result, in collaboration with the University of Toronto, we will conduct a feasibility and acceptability pre-

post study examining the delivery of a remote one-on-one individualized PA programme in adult participants with TRD. Participants who demonstrate interest or are referred from the Interventional Psychiatry Program (IPP) will be offered supervised PA training once a week and unsupervised PA training 2-3 times/week for 4 weeks, plus PA counselling, to enhance motivation to engage in PA without supervision. We will evaluate the PA intervention using a comprehensive public health framework, RE-AIM. This study will target various program indicators including, reach, efficacy, adoption, implementation and maintenance of the PA intervention. In addition to the exit survey, participants will complete a semi-structured qualitative interview with a research team member to better understand their experience of participating in the PA intervention.

## 1.2 Objectives

Over a 13-week (~3-week baseline period, 4-week randomized treatment phase, and 6-week follow-up) period, we will conduct a pilot randomized controlled clinical trial to determine the feasibility of a trial randomizing adult participants with TRD to a remotely delivered one-on-one individualized PA programme in addition to treatment as usual (TAU) or TAU. We will also assess the acceptability of the PA programme. We aim to include the use of a digital platform (i.e., the Oura Ring) to evaluate the effect of the PA programme on digital passive data collected. This study has the following aims:

### Primary Aims:

**Aim 1:** To assess the feasibility (recruitment rate, withdrawal rate, adherence rate, and data completion rate) of randomizing adult participants with TRD to a PA programme add-on to TAU or TAU and to assess acceptability (responses on the exit survey and semi-structured qualitative interviews) of the PA programme.

**H1a (Recruitment rate):** Over 15 months, we will be able to recruit and assess 2 participants per month.

**H1b (Withdrawal rate):** The overall withdrawal rates will be no more than 20%.

**H1c (Data completion rate):** The data completion rates will be more than 80% in both treatment arms.

**H1d (Adherence rate):** Adherence rates, including treatment compliance and study completion, will be more than 80% in both treatment arms.

**H1e (Acceptability):** Participants will report satisfaction with the content and delivery of the intervention, as measured by the exit survey and semi-structured qualitative interview.

If feasibility thresholds are not met, our team will evaluate the reasons and determine whether they could be addressed with protocol modifications.

### **Exploratory Aims:**

**Aim 2:** To monitor the efficacy of the implementation of a 4-week remotely delivered PA programme by assessing the change in depressive symptoms, anxiety symptoms, and quality of life in participants with TRD and calculating the difference between scores at these time points for each group.

**Q2a:** What are the estimates for the standard deviation of Hamilton Depression Rating Scale – 17 item (HAM-D-17) and its within-person correlation between baseline and the end of the 4-week intervention period and between baseline and the end of the 6-week follow up?

**Q2b:** What are the estimates for the standard deviation of Patient Health Questionnaire – 9 item (PHQ-9) and its within-person correlation between baseline and the end of the 4-week intervention period and between baseline and the end of the 6-week follow up?

**Q2c:** What are the estimates for the standard deviation of Generalized Anxiety Disorder – 7 item (GAD-7) and its within-person correlation between baseline and the end of the 4-week intervention period and between baseline and the end of the 6-week follow up?

**Q2d:** What are the estimates for the standard deviation of World Health Organization Well-Being Index – 5-item (WHO-5) and its within-person correlation between baseline and the end of the 4-week intervention period and between baseline and the end of the 6-week follow up?

**Aim 3:** To evaluate the effect of the PA programme on digital physiological passive data collected through the use of a wearable device (Oura Ring).

**Aim 4:** To explore the perceptions and experiences of PA in individuals with TRD across the lifespan.

## **2. METHODS**

### **2.1 Trial Design**

We propose an interventional, randomized, 4-week pilot clinical trial. The trial will enroll 30 participants to generate data for feasibility and acceptability, and to estimate variability of the efficacy outcomes to use in the sample size calculation for future larger scale trials. We will evaluate the feasibility and acceptability of a 4-week remote one-on-one individualized PA programme for participants with TRD (i.e.,  $\geq 2$  failed trials of antidepressant treatment) and in a mild-to-severe major depressive episode (MDE) as measured by a Montgomery-Åsberg Depression Rating Scale (MADRS) total score of  $\geq 7$ , while simultaneously using a digital wearable device (Oura Ring) to monitor participant's physiological data.

Participants will be randomized to one of two treatment arms:

- 1) PA group: Participants in this group will continue TAU and will participate in a 4-week remotely delivered one-on-one individualized PA programme.
- OR
- 2) TAU group: Participants in this group will continue to receive TAU, but will not receive the PA programme add-on. Instead, these participants will be given a handout with the Canadian 24-hour movement guidelines and be told that they are encouraged to engage in PA.

Participants in both groups will use a wearable device, known as an Oura Ring, to collect passive data related to physiological variables (e.g., sleep, heart rate, activity). Please see Section 2.4.2 for more information on the Oura Ring and Section 2.4.1 for a thorough description of the remotely delivered PA programme. **Figure 1** summarizes the proposed study design. Participants in both treatment arms will continue to receive treatment congruent with Canadian Network for Mood and Anxiety Treatments (CANMAT) guidelines with no changes to treatments 28 days before screening. The study team will also try to keep treatments unchanged during the 4-week randomized intervention phase and the 6-week follow-up phase (Sections 2.4.4 and 2.4.5).

At the end of their participation in the study, participants who were randomized to the TAU group will have access to at least one session with a PA trainer.

[figure not shown]

**Figure 1.** Proposed study design. TAU = treatment as usual, PA = physical activity.

## **2.2 Eligibility Criteria**

### **2.2.1 Inclusion criteria**

1. Sedentary adults (engage in less than 60 minutes of moderate-to-vigorous PA per week) between the ages of 18 and 65 years, inclusive, capable of giving informed consent.
2. Participants meeting diagnostic criteria for MDD without psychotic symptoms according to the Diagnostic and Statistical Manual of Mental Disorders - 5th Ed. (DSM-5) and currently experiencing a MDE as confirmed by the Mini International Neuropsychiatric Interview (MINI).
3. A MADRS total score of  $\geq 7$  at screening (mild-to-severe MDE).
4. Failure of at least two trials of antidepressant therapy of adequate dose and duration during the current episode as established by the Antidepressant Treatment History Form (ATHF) and self-report.
5. Receiving treatments congruent with CANMAT guidelines with no changes to treatments one month before screening (28 days).

### **2.2.2 Exclusion criteria**

1. Current symptoms of mania, hypomania, mixed episodes, or psychosis.
2. Have received a diagnosis of alcohol or a substance use disorder within the past 3 months or as confirmed by the MINI. Other secondary psychiatric comorbidities (e.g., anxiety disorders, trauma-related disorders, etc.) will not be excluded.
3. Pregnant females.
4. Acute risk for a cardiovascular event (i.e., cardiovascular event in the past within the past 12 months).
5. Have any medical contraindications to exercise according to the Physical Activity Readiness Questionnaire (PAR-Q).
6. Self-reported balance, gait, or locomotion difficulties that would preclude participation in a PA programme.
7. Have any other condition that, in the opinion of the investigator(s), would adversely affect the subject's ability to complete the study or its measures.
8. Have exercise-induced asthma.
9. Taking medication that interferes with heart rate response to exercise, such as beta blockers.
10. Do not own a smartphone.
11. Do not have reliable access to the Internet.
12. Have previously received intravenous ketamine treatment in the last 2 months.

Non-English-speaking individuals are excluded because the ability to communicate study information, answer questions accurately and completely about the study, and obtain consent are necessary.

## **2.3 Withdrawal Criteria**

Participants are free to withdraw their consent and/or end their participation in the research study at any time without penalty or loss of benefits or treatment to which they are otherwise entitled. Participants may be withdrawn from the study by the participant's doctor if they feel that it is in their best interest.

Participation may also be discontinued if:

- The participant fails to adhere to the study's responsibilities
- The participant meets any exclusion criteria (either newly developed or not previously recognized)
- The participant presents with any severe adverse event (AE)
- Anything, in the opinion of the investigator(s), that would place the participant at increased risk or preclude the participant's full compliance with or completion of the study

If a participant experiences an AE, they will receive the necessary treatments to alleviate any untoward event and will be monitored by the study physician until it is safe for them to be discharged. Participants will be followed up with the next day to monitor the progression of their condition.

Data from a participant who has been withdrawn will be collected up to the next day after the withdrawal to ensure that the participant has no more complications. All data collected before the day of withdrawal will be used for analysis. If a participant withdraws from the study at any time, the reasons for withdrawal will be collected and documented as part of the feasibility outcomes for this study.

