#### **2.4.4 Concomitant medication**

Before the intervention, research staff will document all medications taken by participants on a regular basis. No changes to treatment are allowed one month (28 days) before screening due to the probable impact on psychiatric symptoms. Participation in the study will not alter the standard of care, including any required changes to treatment regimens. While the study aims to avoid any changes to participants' treatment during the 4-week randomized intervention phase and the 6-week follow-up phase, changes that are required clinically to manage an acute clinical deterioration or adverse effects will be allowed and recorded; according to the treat (ITT) principle, participants whose treatment is changed will remain in the trial.

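### Section 2.3 lets staff remove a participant from the study for non-adherence or a newly met exclusion, with data collection ending the next day, and does not say that someone who stops only the programme stays in follow-up

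*Protocol*

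**What the plan says.** **Leaving the study.** Protocol section 2.3 first covers withdrawal by the participant or by the participant's doctor. It then adds: "Participation may also be discontinued if" one of several conditions holds. Two matter here: "The participant fails to adhere" to the study's responsibilities, and "The participant meets any exclusion criteria (either newly developed or not previously recognized". The others are a severe adverse event and the investigator's opinion on risk, compliance or completion.

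**After withdrawal.** "Data from a participant who has been withdrawn will be collected up to the next day after the withdrawal". The stated purpose is to check for further complications. Data from before the day of withdrawal are analysed, and "the reasons for withdrawal will be collected and documented as part of the feasibility outcomes".

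**Treatment changes.** Section 2.4.4 says "changes that are required clinically to manage an acute clinical deterioration or adverse effects will be allowed and recorded". Sections 2.4.4 and 2.4.5 both keep such participants in the trial, citing intention to treat. Two exclusion criteria in 2.2.2 could be newly met through such a change: number 9, "Taking medication that interferes with heart rate response to exercise, such as beta blockers", and number 12, "Have previously received intravenous ketamine treatment in the last 2 months".

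**What the rates feed.** Section 2.5.1 calls a full trial feasible if the upper 95% limit for withdrawal is at most 20% and the lower 95% limits for data completion and adherence are at least 80%. H1d in 1.2 includes study completion in adherence. Section 2.13 adds complete clinical outcome data to the proportion counted as compliant.

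**The concern.** Withdrawal, adherence and data completion are meant to describe different things. Under 2.3, a participant who does not keep up with the programme may be taken out of the study. That one fact then counts as non-adherence, as a withdrawal and as a failure to complete, and it leaves missing outcomes. A discretionary staff decision thus feeds into rates the pilot sets out to measure. The rule in 2.5.1 does not separate staff removals from participants' own withdrawals.

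The next-day stop also costs data. The protocol's stated purposes include estimating variability for a later sample size (2.1) and baseline-to-follow-up correlations by group (2.5.2). A participant with no follow-up score contributes nothing to those correlations. An analysis plan cannot recover assessments that were never made, so the remedy belongs in the protocol.

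**Working it through.** **1. Is there a rule for stopping the programme while staying in the study?** Section 2.3 describes exits from the study only. Section 2.18.7 lists interruption and discontinuation of the intervention among the actions after an adverse event, so the programme can be stopped by itself. That list covers adverse events only and has no follow-up rule. Section 2.12.5 has all participants contacted for the end-of-intervention HAM-D-17, with no adherence condition. Staying in follow-up is therefore possible, but no text states it for someone who stops.

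**2. Outcomes lost.** The timeline in 2.6.1 gives three HAM-D-17, PHQ-9 and GAD-7 assessments: baseline, end of intervention, exit visit. Removal before the end of the intervention keeps the first and loses two.

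- Planned HAM-D-17 assessments: 3 × 30 = 90.
- Two such removals lose 2 × 2 = 4, leaving 86/90 = 95.6%.
- Counted per participant: 28/30 = 93.3%.
- Participants left for a correlation: 28 of 30 overall. By group, if both removals fall in one arm, 18 of 20 (PA) or 8 of 10 (TAU).

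**3. Sensitivity of the withdrawal criterion.** Inputs: n = 30 (2.7) and a 20% ceiling on the upper 95% limit (2.5.1). The protocol gives no removal rate and no interval method, so x is varied and four methods are shown. With p = x/n and z = 1.96:

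- Exact upper limit: Beta quantile at 0.975 (two-sided) or 0.95 (one-sided), parameters x + 1 and n − x.
- Wilson: [p + z²/2n + z√(p(1−p)/n + z²/4n²)] / (1 + z²/n).
- Wald: p + z√(p(1−p)/n). For x = 2: 0.0667 + 1.96 × √(0.0667 × 0.9333/30) = 0.156.

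| Withdrawn of 30 | Two-sided exact | Wilson | One-sided exact | Wald |
|---|---|---|---|---|
| 1 | 17.2% | 16.7% | 14.9% | 9.8% |
| 2 | 22.1% | 21.3% | 19.5% | 15.6% |
| 3 | 26.5% | 25.6% | 23.9% | 20.7% |

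One passes on every method, two depends on the method, and three fails on every method. Lower limits for completion or adherence are the complements, in the same method order: 29/30 gives 82.8/83.3/85.1/90.2%, 28/30 gives 77.9/78.7/80.5/84.4%, and 27/30 gives 73.5/74.4/76.1/79.3%.

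**4. What the change would do.** Suppose three participants stop the programme and, as a best case, all are still assessed.

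- Withdrawal: 0/30, two-sided exact upper limit 11.6%, passes.
- Data completion: 30/30, two-sided exact lower limit 88.4%, passes.
- Adherence: 27/30, below 80% on all four methods, fails.

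If instead all three are removed, withdrawal and adherence both fail on every method. The overall answer is the same in both cases. With the change, the results show that adherence was the problem and the outcome data are kept.

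**The case against.** The best counter-argument is that nothing in 2.3 compels removal. Every staff ground is permissive, 2.18.7 treats stopping the intervention as a separate action, and 2.12.5 contacts everyone. The revision history also records that a rule excluding participants who missed more than one supervised session was deleted to reduce drop-out. The next-day sentence is a safety check on people already withdrawn. All of this stands. A reader might infer that the protocol closes off any way to stop the programme and stay, or that removal for non-adherence is automatic. The text supports neither: what is missing is an explicit statement.

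A reader might also infer a flat contradiction between 2.3 and the intention-to-treat sentences in 2.4.4 and 2.4.5. The overlap is narrow. It arises only when exclusion 9 or 12 is met through a clinically required treatment change, and staff can follow both sections by not using the discretion. The wording is awkward because 2.3 does not say which governs.

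Other points also have weight. Reasons for withdrawal are recorded, and the team will review causes if a threshold is missed, so staff removals could be described afterwards. Removals for safety are real feasibility information. No comparative analysis of clinical outcomes is planned, so the lost scores bias no treatment comparison. The table shows the effect of any one to three withdrawals, whatever their cause. It also pools the arms, while H1c and H1d speak of both arms (20 and 10 participants). What these points leave standing is that outcomes not collected cannot be recovered, and that the 2.5.1 rates mix two kinds of exit.

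**Conclusion.** The point holds as a cheap improvement to a conduct rule. Section 2.3 gives staff a discretion which, when used for non-adherence, turns one event into failures on adherence, withdrawal and completion. It also ends outcome collection before the end-of-intervention assessment, the exit visit or both.

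The size is conditional. No number of removals follows from the protocol. At a pooled 30, the withdrawal criterion turns on the second removal under two-sided exact or Wilson limits, and on the third under one-sided exact or Wald limits. The effect on data completion depends on whether completeness is counted per participant (93.3% after two early removals) or per assessment (95.6%).

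It would be tempting to conclude that the present wording could wrongly fail the trial as a whole and that the change would rescue it. The documents do not support that. In the example with three programme stops, adherence fails with or without the change. The gain is that the feasibility rates are separated and the outcome data are retained.

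**What to change.** In section 2.3:

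- Make non-adherence or a clinical stop a reason to discontinue the programme, not the study. The TAU arm has no programme to stop, so there record the non-adherence and continue follow-up.
- Continue the scheduled end-of-intervention and follow-up week-6 assessments and the adverse event log, unless the participant withdraws consent to data collection.
- State that 2.4.4 and 2.4.5 take precedence over the exclusion-criteria ground when the criterion is met through a treatment change they cover. The programme may still be stopped for safety.
- Count those who stop the programme as non-adherent, not withdrawn, and report staff-initiated stops separately from participants' own withdrawals.

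The cost is protocol and consent wording and a few extra assessments. The end-of-intervention HAM-D-17 is already done over Zoom and the questionnaires through REDCap; the exit visit is in person. Some who stop may decline later assessments, so retention will not be complete.
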